#### Instruments

##### Gamified Web App

A gamified web app was developed in the first study to prospectively follow-up participants and monitor cannabis and tobacco use, as well as identify withdrawal symptoms (see Table 1). The game of the gamified web app was named DuCATA: Your heroic journey deserves to be told (the original name is “DuCATA: Tu viaje heroico merece ser contado”).

**Table 1 table1:** Variables included in the web app to monitor tobacco and cannabis use.

Frequency	Variable	Description
Every 72 hours	Tobacco use in the last 48 hours	Have you used tobacco in the last 48 hours, with or without cannabis?
Every 72 hours	Cannabis use in the last 48 hours	Have you used cannabis in the last 48 hours?
Every 72 hours	Number of joints	How many joints have you consumed in the last 48 hours?
Every 72 hours	Cannabis reduction	Compared to 2 days ago, have you reduced your cannabis use?
Every 72 hours	Cannabis withdrawal checklist	Have you experienced any of these symptoms in the last 48? Shakiness or tremulousness Depressed mood Decreased appetite Nausea Irritability Sleep difficulty Sweating Craving to smoke marijuana Restlessness Nervousness or anxiety Increased aggression Headaches Stomach pains Strange dreams Increased anger

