#### Inclusion Criteria

Participants must be older than 18 years of age, daily cannabis users regardless of tobacco consumption pattern or type, in treatment for cannabis use or another substance in an SAP, followed by collaborating clinicians, own a smartphone or computer with an internet connection, commit to daily participation in the web app for 6 weeks, have and use WhatsApp (Meta Platforms) and email, and provide informed consent.

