#### Cannabis Use

Cannabis use is determined based on the (1) consumption of cannabis in the last 48 hours (yes or no), reduction of cannabis in the last 48 hours (yes or no), and cannabis abstinence or reduction requiring a cannabis withdrawal test and (2) cannabis product used (hashish, marijuana, etc), mode of administration (smoking, snorting, ingestion, etc), frequency of cannabis use in the last month and week, type of use (alone, accompanied, and both), and reasons for use (addiction, recreational, social, sleeping, etc).

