#### Statistical Methods

For independent variables, a descriptive analysis will be conducted, including frequencies, percentages, and their 95% CIs. To assess effectiveness measures such as changes in cannabis-tobacco use, withdrawal syndrome, and treatment adherence, frequencies and percentages will be described for baseline and main assessment end points according to the four patterns of cannabis use and they are (1) concurrent, (2) sequential concurrent, (3) asynchronous concurrent, and (4) exclusive cannabis. Incidence rates of abstinence and symptomatology will be calculated for the same assessment end points across the 4 patterns. The RR of quitting or reducing cannabis and tobacco, as well as quit attempts for both substances (95% CI), adjusted for independent variables, and initial consumption pattern, will be calculated using Cox or Poisson robust regression models. Predictive analysis techniques including logistic regression and random forest will be used to model the probability of events occurring based on other factors. Time series analysis will be used to observe consumption trends during the follow-up, and survival analysis of recurring events will be conducted to observe abstinence or reduction processes among participants.

For all analyses, SPSS (IBM Corp) for Windows version 21, Python (version 3; Python Software Foundation), R (version 4.0.3; R Core Team), and scikit-learn will be used. The level of significance will be set at 5% (*P*<.05).

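### The app counts cannabis amount only in joints, so use by another route enters any amount trend as a false zero or false fall; the yes/no use and reduction items are unaffected

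*Protocol article*

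**What the plan says.** Table 1 (Gamified Web App) lists three cannabis-use items, each asked every 72 hours:

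- any use: "Have you used cannabis in the last 48 hours" (yes or no);
- amount: "How many joints have you consumed in the last 48 hours";
- self-judged reduction: "Compared to 2 days ago, have you reduced your cannabis use" (yes or no).

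The joint count is the only one of these that gives a quantity.

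The Cannabis Use section gives the 48-hour outcomes as "consumption of cannabis in the last 48 hours (yes or no), reduction of cannabis in the last 48 hours (yes or no"). Among further variables it lists "mode of administration (smoking, snorting, ingestion, etc), frequency of cannabis use in the last month and week". The End Points section is wider: it makes the variables reported in the app every 3 days end points, and the joint count is one of them.

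The Inclusion Criteria admit "daily cannabis users regardless of tobacco consumption pattern or type". In that phrase, type refers to tobacco. What matters here is that neither the inclusion nor the exclusion criteria limit the route of cannabis use.

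Statistical Methods states: "Time series analysis will be used to observe consumption trends during the follow-up". It does not say which variable carries the trend.

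**The concern.** A joint count measures amount only for people who smoke joints. The study admits users of other routes and records those routes elsewhere, but the app has no place to enter an amount for them. A participant who answers as worded gives yes for use and 0 for joints. As an amount, that 0 is wrong.

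Two kinds of participant are affected. A steady non-joint user contributes a flat line at zero. A participant who moves from joints to another route contributes a fall that did not happen. In a study of people trying to reduce or quit, a false fall looks like the behaviour change the study wants to describe. What is at stake is the direction and size of any trend in amount over the six weeks.

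**Working it through.** The plan states no figure on this point, so there is nothing to reproduce. The check sets the items side by side and follows the possible answers through them. The 8 joints per 48 hours used below is an illustrative assumption.

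| Participant (true total use unchanged) | Use item | Joint count | Change in recorded amount |
|---|---|---|---|
| Joints throughout | yes | 8, then 8 | none |
| Non-joint route throughout | yes | 0, then 0 | none, but the level is falsely zero |
| Full move from joints to another route | yes | 8, then 0 | (8 − 0)/8 = 100% fall |
| Half of joints replaced by another route | yes | 8, then 4 | (8 − 4)/8 = 50% fall |

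**What is not affected.** The use item stays at yes in every row, so nobody is wrongly counted as abstinent. The reduction item asks about cannabis use as a whole, so its answer does not depend on the joint count. The Cannabis Use section defines reduction through that item. The relative risk of quitting or reducing is therefore outside the problem as long as reduction is taken from it.

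**What can be detected.** A yes for use with 0 joints marks non-joint use, or an inconsistent answer, at each report. A partial switch (last row) leaves no such mark, because the joint count stays above zero.

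**Whether mode of use recorded elsewhere fills the gap.** Six weeks at one report every 3 days gives 42/3 = 14 app reports. Table 2 in the Monitoring Software section ticks type and way of use at baseline after acceptance and, as the broken table reads, at 18 days. The End Points section says software variables are collected at baseline and every 6 days. Three readings are possible:

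- Mode asked once, at day 18: the remaining 42 − 18 = 24 days, or 24/3 = 8 reports, have no later mode record.
- Mode asked every 18 days: 18/3 = 6 app reports per mode record.
- Mode asked every 6 days: 6/3 = 2 app reports per mode record.

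On none of these readings is route known at each app report.

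**Effect on a group mean (assumption, not an estimate).** Suppose a share s of a group moves fully to another route, their baseline count equals the group mean, and nobody's true use changes. The false fall in the mean is then s × 100%. With s of 5%, 10% and 20%, a mean of 8 becomes 7.6, 7.2 and 6.4, which are falls of 5%, 10% and 20%. The documents give no value for s.

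**The case against.** The strongest reply is that the joint count hardly matters. The Cannabis Use section does not name it among the 48-hour outcomes. Reduction has its own route-neutral question. No comparison of joint counts across the four patterns is specified, and the phrase on consumption trends does not mention joints. The introduction also describes the joint as the commonest way of using cannabis in Europe, so it is a reasonable unit for this cohort.

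Much of this stands, and it confines the point to amount. It does not remove the point. The End Points section includes app variables generally, Table 1 lists the joint count among them, and a trend in amount from app data has no other numeric source. The reduction item cannot stand in for it: it is a yes/no judgement against two days earlier and gives neither the size of a change nor the change since treatment began.

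A second reply is that handling a yes with 0 joints belongs in an analysis plan. That is fair for the rule itself, but not for the app item: without a route tick, a partial switch cannot be recovered in analysis.

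A reader might go further and infer that amounts cannot be compared across the four patterns, because concurrent use is defined by the mixed joint and other routes would gather among exclusive cannabis users. The documents do not support this. The patterns are defined by how tobacco is combined with cannabis, exclusive users may also smoke joints, and no data on route by pattern are given. Nor can one say that a switch goes unseen for at most 18 days, since Table 2 and the End Points section leave the timing of the mode question open.

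**Conclusion.** The point holds for amount and its trends only. For an affected person the error is complete (a level of 0, or a 100% fall after a full switch) or partial (50% if half the joints are replaced). At group level its size is unknown. It depends on how many participants use or move to other routes, which the documents do not report, and it may be small if joints dominate in this cohort. Whether it differs between patterns is also unknown.

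The conclusion assumes that participants answer the items as worded and that some trend in amount will be drawn from the joint count. It does not call abstinence, self-reported reduction or the relative risk of quitting or reducing into question. This is a correctable measurement limitation, optional to low in priority.

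**What to change.** - Keep the joint item exactly as it is, so that the series stays intact. Replacing it with a count of occasions by any route would break the series and would treat an ingested dose as equal to a joint.
- Add one tick to the same report for any non-joint cannabis use in the same 48-hour window.
- Treat amount as missing, not zero, whenever use is yes and joints are 0. Report how many such reports occur, by pattern.
- Report joint-count trends only for participants whose recorded mode is joints, as change within person, and state that they describe joint use and not total cannabis amount.

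The cost is one extra tick per report and a short analysis rule. The tick cannot be recovered for participants already followed. By June 2024, 74 had been enrolled towards the target of 150 given in Results, leaving 150 − 74 = 76 still to come at that date. For earlier participants only the missing-amount rule and the software's mode records are available, so partial switches would stay hidden. A few participants would leave the joint-trend analysis. They would not be a random subset, which is why their number should be shown.

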### Primary Quantitative Effectiveness Outcomes of the Web App in Monitoring Behavioral Changes

#### End Points

The end points are (1) variables reported every 3 days during 6 weeks within the web app and (2) variables collected in the external software at baseline and every 6 days.

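### The only stated measure of cannabis reduction uses a moving 2-day reference, so it cannot tell a sustained partial reduction from ordinary fluctuation

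*Protocol article*

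**What the plan says.** Table 1 (Instruments, Gamified Web App) lists cannabis reduction as a yes/no question asked every 72 hours: "Compared to 2 days ago, have you reduced your cannabis use". At the same times the app asks "How many joints have you consumed in the last 48 hours" and, separately, whether any cannabis was used in the last 48 hours.

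End Points makes the app items end points: "variables reported every 3 days during 6 weeks within the web app". The Cannabis Use outcome lists "reduction of cannabis in the last 48 hours (yes or no" and adds "cannabis abstinence or reduction requiring a cannabis withdrawal test".

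Statistical Methods plans "The RR of quitting or reducing cannabis and tobacco, as well as quit attempts for both substances (95% CI), adjusted for independent variables", by Cox or robust Poisson regression, and "survival analysis of recurring events will be conducted to observe abstinence or reduction processes among participants".

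The article does not define reduction against baseline, give it a minimum size, or say that it is derived from the joint count.

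**The concern.** A reduction outcome among people entering treatment should show whether they use less than they did before. This item asks whether they use less than two days earlier. Once use has stepped down and levelled off, the comparison is between two equally low periods. A person whose average never changes still has higher and lower days, and each lower one can produce a yes.

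At stake are the analyses of reducing cannabis use. If they rest on this item, a relative risk comparing the four use patterns would largely compare how much use fluctuates, and a true difference in sustained reduction would be pulled towards no effect.

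**Working it through.** **From the article.** Reports every 3 days for 6 weeks: 42 / 3 = 14 reports. One yes/no item with a reference 2 days back and no size threshold.

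**Assumed, because the article gives no joint counts.** 2 to 10 joints/day, independent Poisson daily counts, and a yes whenever the recent count is at least one joint below the earlier one. Both kinds of participant are put through the same model.

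**Step 1, wording alone.** Use falls once and then stays level. At every later report, current use equals use 2 days earlier, so the literal answer is no. This needs no count assumption.

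**Step 2, with day-to-day variation.** If both windows have the same mean m, then P(yes) = (1 − T) / 2, where T = exp(−2m) × I0(2m) is the chance of a tie and I0 is the modified Bessel function.

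| Windows compared | Unchanged user | Settled after reducing |
|---|---|---|
| One day with one day | 10/day: m = 10, T = 0.090, P = 45.5% | 5/day: m = 5, T = 0.128, P = 43.6% |
| 48 h with preceding 48 h | 5/day: m = 10, T = 0.090, P = 45.5% | 2/day: m = 4, T = 0.143, P = 42.8% |

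For 48-hour windows and unchanged use of 2 to 10 joints/day, P runs from 42.8% to 46.8%.

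**Step 3, over the whole follow-up (48-hour windows).**
- Unchanged at 5/day: 14 × 0.455 = 6.4 expected yes answers.
- Sustained fall from 5 to 2/day: the first report after the fall catches it with probability P(Poisson(4) < Poisson(10)) = 93%, if its windows fall cleanly either side of the change. If that is the first of the 14 reports, the expected number is 0.93 + 13 × 0.428 = 6.5.
- The two recurrent-event counts are practically equal.
- The first yes in the unchanged user comes after about 1 / 0.455 = 2.2 reports, or 2.2 × 3 = 6.6 days. Treating reports as independent, at least one yes in 14 has probability 1 − (1 − 0.455)^14 > 99.9%.

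**Step 4, a fixed reference on the same data.** Take a baseline of 10 joints per 48 h and, only as an example, call 5 or fewer a reduction.
- Unchanged: P(Poisson(10) ≤ 5) = 6.7%.
- Settled at 2/day: P(Poisson(4) ≤ 5) = 78.5%.

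This treats the baseline as known without error.

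**Step 5, sensitivity.** Suppose participants say yes only to a fall of at least 25% between 48-hour windows. Summing the Poisson probabilities over pairs that meet this gives 28% of reports for the unchanged user at 5/day and 37% for the reducer settled at 2/day. That gap comes from larger relative variation at low counts, not from recognition of the sustained fall.

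**The case against.** **The source of the outcome is not named.** Statistical Methods does not say which variable supplies reducing. It refers to tobacco as well, and Table 1 has no tobacco-reduction item, so at least that part must come from elsewhere. Joint counts are collected, and a fuller analysis plan may derive reduction from them. This stands as a limit: the link from item to model is the natural reading, not an explicit statement. It does not remove the point, because the article names the app items as end points and gives this as its only measure of cannabis reduction.

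**The short window has a use.** The Introduction places withdrawal onset 2 to 4 days after a reduction, and the Cannabis Use section ties the withdrawal test to abstinence or reduction. A recent-change question suits that purpose. This stands, and is a reason to keep the item.

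**Self-report is not arithmetic.** Some participants will ignore a one-joint difference, or say yes because they are keeping to an earlier cut. This stands against any exact percentage. It also means that the same answer has different meanings across participants.

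**Stronger readings that a reader might infer.**
- That people who quit are lost from the outcome. They are not: the separate 48-hour use item records them at every report, and the analysis is of quitting or reducing.
- That Cox models would have no contrast because nearly everyone has an event. Event times still differ; the trouble is that much of the difference would be chance.
- That a sustained reducer is coded reduced only once in 14 reports. That holds only if use is perfectly constant. With the variation granted to the unchanged user, it is about 43% to 44% of reports. The consistent result is failure to discriminate, not a penalty on sustained change.

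**Conclusion.** The point holds in this form: the article's only stated measure of cannabis reduction has a moving reference and does not separate a sustained partial reduction from unchanged, fluctuating use. Under one Poisson model with 5 to 10 joints/day, both kinds of participant answer yes at roughly 44% to 45% of reports. These rates depend on assumed counts, independent days and literal answering. That the reference moves and loses a maintained reduction follows from the wording.

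The effect is confined to the analyses of reducing cannabis use, where estimates would be diluted by noise and time to first reduction would largely reflect chance timing. Abstinence outcomes are unaffected. The correction should be made, and the data for most of it are already collected.

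**What to change.** For the reduction analyses, state that cannabis reduction is derived from joints per 48 hours, already collected every 72 hours, against a fixed reference for each participant: baseline or pre-treatment use if a count is held, otherwise the first app report. Analyse the continuous percentage change. If a binary outcome is needed, prespecify a threshold and require it over consecutive reports; the half-of-baseline cut-off above is only an example. Keep the 2-day item as descriptive and for timing withdrawal symptoms.

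The cost is analysis wording plus confirmation of one baseline value. Four limits should be stated:
- Table 2 lists a baseline cannabis use pattern but not explicitly a joint count, so its existence must be checked.
- The Recruitment section says that participants have already begun to reduce or quit, so a reference taken at entry may understate the change.
- A single first app report is a noisy reference.
- Joint counts miss the non-smoked routes listed under Cannabis Use, and 48-hour windows every 72 hours cover 14 × 2 = 28 of the 42 days.

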##### Monitoring Software

The monitoring software was designed to record participants’ recruitment, obtain their baseline information, and periodically send additional questionnaires to assess participant behavior, contextual factors, and so forth (see Table 2). This software was created to carry out the study, and we have named it DuCATA software.

**Table 2 table2:** Baseline and follow-up variables regarding sociodemographic characteristics, tobacco, cannabis use, attitudes, social norms, and motivation to quit of the participants (variables included in the monitoring software).

Variables				Temporality						
				Baseline before acceptance	Baseline after acceptance	6 days software	18 days software	Final software		
**Dependent variables**										
		**Cannabis addiction**		✓	✓	✓		✓		
			Cannabis use pattern	✓	✓	✓				
			Dependency severity		✓	✓				
			Cannabis type and way of use		✓		✓			
			Cannabis withdrawal symptoms		✓	✓				
		**Addiction to tobacco**		✓	✓			✓		
			Tobacco use pattern		✓	✓				
			Nicotine dependence		✓	✓				
		Alcohol addiction			✓	✓				
		**Attitudes**			✓					
			Psychoemotional factors		✓		✓			
			Social environment		✓		✓			
		**Subjective perception of norms**			✓		✓			
			Beliefs and expectations of consumption and treatment					✓		
		Self-efficacy			✓	✓				
		Level of approach in smoking or cannabis received			✓			✓		
		**Motivation**				✓				
			Cannabis dropout							
			Tobacco dropout			✓				

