#### Objective 3 (Second Study)

Analyze changes in tobacco use during the cannabis treatment process based on the identified typologies of cannabis-tobacco users and the level of clinical care they receive (with or without assistance for quitting tobacco).

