#### Sample Size

According to a recent meta-analysis, the probability of cannabis cessation in this patient population treated using diverse therapeutic approaches is relative risks (RR)=1.48 (28). Given its heterogeneity, we will use a more conservative estimate (RR=1.20). Thus, with an alpha risk of 0.05, a beta risk of 0.20 in a bilateral contrast, and accounting for 20% losses to follow-up, 282 participants will be required. Approximately 2000 people start treatment for cannabis use each year in Catalonia [28], making it feasible to recruit 282 participants within a 1-year period.

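### Help to quit tobacco, the comparison in Objective 3, is recorded only at baseline and at the end, undated, so help begun in between cannot be ordered against tobacco change

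*Protocol article*

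**What the plan says.** Objective 3 (Second Study) analyses changes in tobacco use during cannabis treatment by user typology and by "the level of clinical care they receive (with or without assistance for quitting tobacco").

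Table 2 (Monitoring Software) has five time columns: baseline before acceptance, baseline after acceptance, 6 days, 18 days and final. The row for the care received, "Level of approach in smoking or cannabis received", is ticked under baseline after acceptance and under final. It has no tick under 6 or 18 days. The table places it among the dependent variables. The Independent Variables section does not list it, and no start date of assistance is mentioned.

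Tobacco use is followed much more closely. Table 1 (Gamified Web App) asks every 72 hours: "Have you used tobacco in the last 48 hours, with or without cannabis". Table 2 also ticks tobacco use pattern under baseline after acceptance and 6 days.

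The End Points section gives a general schedule that does not match the row on care: "variables reported every 3 days during 6 weeks within the web app" and "variables collected in the external software at baseline and every 6 days".

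Statistical Methods plans "The RR of quitting or reducing cannabis and tobacco, as well as quit attempts for both substances (95% CI), adjusted for independent variables" and for initial consumption pattern, from Cox or robust Poisson models, together with survival analysis of recurring events. It does not name assistance. Sample Size allows for losses: "accounting for 20% losses to follow-up, 282 participants will be required".

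**The concern.** The outcome is dated to within about three days, but care received during follow-up is captured once, at the end. A final answer that help was received does not show whether it came before or after tobacco use changed. A participant who stops tobacco in week 1 may never be offered help and would then count as unassisted. A participant helped in week 5 must have stayed in care that long and, if help is given only to smokers, must still have been smoking.

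The two values that could form the groups each have a fault:

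- **Final value.** All six weeks are classified by something learned at the end. Time and events before help are then credited to the assisted group, or early quitters collect in the unassisted group.
- **Baseline value.** The order is clear, but help begun later counts as none. The groups then do not reflect care received during treatment, which is what Objective 3 asks about.

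An analysis plan could choose between these values, but it cannot recover timing that was not collected. For this reason the point is not a detail that can be left to a later document.

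**Working it through.** **1. Recording occasions.** Follow-up is 6 weeks, or 42 days.
- Tobacco use in the web app: 42 / 3 = 14 reports.
- Software questionnaires, if sent every 6 days as End Points says: 42 / 6 = 7 occasions.
- Level of approach received, by the ticks in Table 2: 2 occasions, only one of them after baseline. This holds whether the 6-day and 18-day columns mean a single day or a repeating interval, because the row is empty in both.

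**2. Missing final value.** At the planned 20% losses:
- 0.20 × 282 = 56.4, about 56 participants.
- 0.20 × 150 = 30 participants, using the enrolment target in the Results section.

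These participants keep the baseline value.

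**3. Size of the possible bias if the final value forms the groups.** The article gives no rate of tobacco quitting or of assistance, so the rates here are assumptions: p_q = 10%, 20% or 30% quit tobacco by day 42; p_a = 30% or 50% would be offered help by day 42 if still eligible. Hazards are constant, the two times are independent, and help has no effect.

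*Scenario A: help goes only to those still smoking.*
- Cumulative hazards: h_q = −ln(1 − p_q), h_a = −ln(1 − p_a).
- Either event by day 42: S = 1 − (1 − p_q)(1 − p_a).
- Quit before any help: B = S × h_q / (h_q + h_a).
- Ever helped: H = S × h_a / (h_q + h_a).
- Helped, then quit: p_q − B.
- Ever/never risk ratio: RR = [(p_q − B) / H] / [B / (1 − H)].

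For p_q = 0.20 and p_a = 0.30: h_q = 0.2231, h_a = 0.3567, S = 0.44, B = 0.1693, H = 0.2707. The risk is 0.0307 / 0.2707 = 0.113 in the helped and 0.1693 / 0.7293 = 0.232 in the others. RR = 0.49.

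For p_q = 0.20 and p_a = 0.50: h_a = 0.6931, S = 0.60, B = 0.1461, H = 0.4539. The risks are 0.0539 / 0.4539 = 0.119 and 0.1461 / 0.5461 = 0.268. RR = 0.44.

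| Quit by day 42 | RR, help 30% | RR, help 50% |
|---|---|---|
| 10% | 0.46 | 0.41 |
| 20% | 0.49 | 0.44 |
| 30% | 0.52 | 0.48 |

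The true value is 1.0 throughout. A simulation with 2,000,000 participants gave the same range, 0.41 to 0.52.

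*Scenario B: help is offered regardless of quitting.* The times are independent, so the risk of quitting is p_q in both groups and RR = 1.0. The share of quits in the helped group that came before help is [B − p_q(1 − p_a)] / (p_q × p_a). For 20% and 30% this is (0.1693 − 0.14) / 0.06 = 0.49. For 20% and 50% it is (0.1461 − 0.10) / 0.10 = 0.46. Over all six combinations it is 0.45 to 0.50. If help instead starts uniformly over the 42 days and 30% quit, it is about 0.53. The ratio is not shifted under this null, but about half of the quits in the helped group cannot be due to the help.

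**4. If the baseline value forms the groups.** Neither distortion arises. The cost is that help begun after baseline is misclassified as none, to an extent that the article gives no figures to estimate.

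**The case against.** The strongest reply is that no faulty analysis is stated. The article nowhere says that the final value forms the groups, and the adjusted risk ratios in Statistical Methods do not name assistance, so they cannot be read as assisted-versus-unassisted ratios. Objective 3 can be read as stratified description, and the article acknowledges its observational nature as a limitation. This stands: a reader might infer that tobacco change before help *will* be credited to help, but the documents support only that it *could* be.

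A reader might also infer that early leavers have no exposure at all. They do not lack it entirely: the baseline tick applies to them, and only the value for care during follow-up is missing. Nor is it documented that help has mostly not begun at baseline. Method and Cohort Members describe people beginning treatment, but Recruitment and Inclusion Criteria admit people already reducing cannabis or in treatment, including for another substance.

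On size, a reader might infer a strong bias in either direction. The ratio of 0.4 to 0.5 needs help to stop at quitting, a rule that appears nowhere in the article. With independent help the ratio is 1.0, and no scenario worked here gives a ratio above 1.

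Finally, End Points says that software variables are collected every 6 days, and Table 2 is not wholly reliable on timing. The cannabis dropout row has no tick, and the tobacco addiction heading has a final tick that its sub-rows lack. If the item is in fact sent every 6 days, correcting Table 2 would largely settle the matter. None of this supplies a date for help on the schedule as printed.

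**Conclusion.** The point holds as a gap in measurement. On the schedule in Table 2, help to quit tobacco begun after baseline cannot be ordered against tobacco change, and it is unknown for the roughly 20% expected to lack a final questionnaire. Both available groupings are unsatisfactory: the final value risks immortal-time or reverse-order bias, and the baseline value counts later help as none.

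The size depends on facts that the article does not give. The risk ratio of 0.41 to 0.52 under no effect rests on assumed quit and help rates, constant hazards and help reaching only continuing smokers. It shows what could happen and does not predict this cohort's result. One stated objective is affected, not the study as a whole. The change is worth making because it is cheap and the timing cannot be reconstructed reliably afterwards.

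**What to change.** 1. Reconcile the Table 2 row with the 6-day schedule in End Points, and state when this item is asked.
2. Add one item to the existing 6-day questionnaire: whether help to quit tobacco was received since the last questionnaire, with the date.
3. Analyse assistance as time-varying. A participant counts as unassisted until help is first reported, and only tobacco change after that point counts as assisted. The Cox and recurrent-event models already planned can take such a covariate.
4. For those already enrolled (74 by June 2024), ask the date of first assistance at the final questionnaire or obtain it from the recruiting clinician.

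The cost is a small extra response burden and one time-varying covariate. Dates obtained in retrospect may carry recall error. Time-varying coding corrects the order of events. It does not remove differences between people who are and are not offered help, so the comparison remains observational.
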